### Setting and study sample

The recruitment strategy will be performed by General Practitioners (GPs) from primary health centers of the four Spanish regions involved in the study (Andalucía, Aragon, Islas Baleares and Comunidad Valenciana). Inclusion criteria are: older than 18 years, DSM-5 diagnose of Major Depression or Dysthymia, mild or moderate depression expressed as score lower than 14 in the Patient Health Questionnaire (PHQ) [29], depressive symptoms presented for at least two months, be able to read and understand Spanish language and enough capacity for understanding and signing the written informed consent form. Exclusion criteria includes any diagnose of disease that may affect central nervous system (brain pathology, traumatic brain injury, dementia, etc.), any psychiatric disorder other than Major Depression, Dysthymia, anxiety disorders or personality disorders, any medical, infectious or degenerative disease that may affect mood, presence of delusional ideas or hallucinations consistent or not with mood, and suicide risk.

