### Randomization, allocation and masking of study groups

Each patient will be allocated to either one of the four groups using a computer-generated random number sequence. We will use block allocation, with 4 blocks (one for each participating region) including 60 patients per block, with about 60 patients per arm. The allocation will be carried out by an independent researcher, belonging to REDIAPP (Research Network on Preventative Activities and Health Promotion), who is not involved in the study. The method used to implement the random allocation sequence will be a central telephone. The sequence will be concealed until interventions are assigned. Patients will agree to participate before the random allocation and without knowing which treatment they will be allocated to. Study personnel conducting psychological assessments will be masked to participants’ treatment conditions.

The researcher that administers baseline assessments will be unaware of the treatment group to which the patient belongs to. This researcher will be different from the one that administer the questionnaires over the study. GPs will be also unaware, as long as possible, of the arm to which the patient has been randomized, since their treatment should be exclusively based on the recommendations of the guides for the treatment of depression. The flowchart of the study is summarized in Figure 1.

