**Table 1 Tab1:** **Study variables**

**Instrument**	**Assessment area**	**Time of assessment**	**Applied by**
MINI Neuropsychiatric interview	Psychiatric diagnosis	Baseline	Researcher A
PHQ-9	Severity of depression	Baseline and follow-up sessions*	Researcher A (baseline) Online (follow-up sessions)
Sociodemographic data	Gender, age, marital status, education, occupation, economical level	Baseline	Researcher A
SF-12 Health Survey	Health-related quality of life	Baseline and follow-up sessions*	Online
CRSI	Health and social services use	Baseline and 6 and 12 post-treatment months	Researcher A (baseline) Researcher B (6 and 12 post-treatment months)
EQ-5D	Health related quality of life	Baseline and 6 and 12 post-treatment months	Online
PANAS	Positive and negative affect	Baseline and 6 and 12 post-treatment months	Online
FFMQ	Facets and factors of mindfulness	Baseline and 6 and 12 post-treatment months	Online
PHI	Remembered and experienced well-being	Baseline and 6 and 12 post-treatment months	Online

*Follow-up sessions: Post-treatment, 6 and 12 post-treatment months.

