#### Main outcome

The primary outcome will be depressive symptom severity assessed via PHQ-9 [34] using the Spanish validated version [29]. This is an instrument for diagnosis and measuring the severity of depression. PHQ-9 is brief and it is completed by the patient. It will be registered at four times: baseline, post-treatment, 6 month follow-up, and 12 month follow-up.

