### Analysis strategy

#### Analysis of clinical efficacy

Intention-to-treat and per-protocol analysis will be used. Analysis will include the description and “head-to head” comparison between the four groups. Descriptive statistics of the included variables (mean and 95 per cent confidence interval for normally distributed quantitative variables; and median and interquartile range for abnormally distributed quantitative variables) will be performed. To confirm main hypothesis, all variables will be compared (t0-tk) using an analysis of variance (ANOVA) and post-hoc tests or Kruskal-Wallis non-parametric tests. Finally, more sophisticated multivariate analysis, including multilevel regression, will be used. The effect size of improvement and intention-to-treat (ITT) will be estimated.

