#### Cost-utility analysis

Cost-utility will be explored through the calculation of incremental cost-effectiveness ratios (ICER), defined as the ratio between incremental costs and incremental effects measured on QALYs or EQ VAS [50]. QALYs were approximated by using the area under-the-curve technique.

To estimate the incremental cost effectiveness ratio - ICER (marginal incremental cost and incremental effects) the following equation is used:$$ ICER=\frac{Cost\  strategy\ 1- Cost\  strategy\ 2}{effectiveness\  strategy\ 1- effectiveness\  strategy\ 2} $$

Cost-effectiveness acceptability curves (CEACs) will also be plotted when necessary [50]. CEACs display the probability that the intervention is cost-effective, given a varying threshold for the willingness to pay for each QALY gained. The curves obtained incorporate the uncertainty that exists around the estimates of incremental costs and incremental effects associated with the intervention [51].

Data collection will be performed using EXCEL software and then for statistical analysis we used the SPSS (SPSS Inc., Chicago, IL, USA) software version 20, licensed for University of Malaga.

Frequency and proportions used for descriptive statistics of categorical or qualitative variables. For quantitative variables the mean and standard deviation were obtained.

For inferential statistical test Chi-square test for qualitative variables for qualitative and quantitative variables was used test one-way ANOVA, and for the test of the T-Student quantitative variables. In all cases statistical significance corresponded to a value of p <0.05.

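### Free improvement: adjust the confirmatory PHQ-9 comparison for baseline PHQ-9 and region, in one named model, instead of ANOVA or Kruskal-Wallis on t0-tk

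*Protocol article*

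**What the plan says.** The section Analysis of clinical efficacy names the confirmatory test: "To confirm main hypothesis, all variables will be compared (t0-tk) using an analysis of variance (ANOVA) and post-hoc tests or Kruskal-Wallis non-parametric tests". A later sentence adds: "Finally, more sophisticated multivariate analysis, including multilevel regression, will be used". That regression is given no covariates, no levels and no confirmatory role. The statistical paragraph closing the Cost-utility analysis section again refers to one-way ANOVA: "for qualitative and quantitative variables was used test one-way ANOVA".

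Two other sections bear on this choice. Under Main outcome, PHQ-9 is measured before and after treatment: "It will be registered at four times: baseline, post-treatment, 6 month follow-up, and 12 month follow-up". Under Randomization, allocation and masking of study groups, allocation is organised by region: "We will use block allocation, with 4 blocks (one for each participating region) including 60 patients per block, with about 60 patients per arm". Baseline PHQ-9 and region should therefore be known for every randomised patient.

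Setting and study sample restricts the baseline score: "mild or moderate depression expressed as score lower than 14 in the Patient Health Questionnaire (PHQ").

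**The concern.** Read as change from baseline, t0-tk forces a slope of 1 on baseline PHQ-9 instead of estimating the slope from the data. Unless the true slope happens to be 1, some residual variance that baseline could explain stays in the error term. Region, used to block the allocation, also stays in the error term.

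The choice between ANOVA and Kruskal-Wallis has no stated trigger. The two answer different questions: a difference in means, or a comparison of ranks. The rank test takes neither baseline nor region into account, and gives no estimate in PHQ-9 points to set against the 5-point difference that the Sample size section calls clinically significant.

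What is at stake is precision and a clear primary estimate. The validity of the comparison is not in question.

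**Working it through.** **Inputs from the protocol (Sample size; Setting and study sample).** SD 9.2; ITAU mean 16.2; mindfulness mean 10.3, so a difference of 5.9; two-sided alpha 0.05; 60 per arm with 25% loss, so 60 × 0.75 = 45 completers per arm; entry PHQ below 14.

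**Inputs the protocol does not give (assumed, shown as ranges).** Correlation rho between baseline and follow-up PHQ-9: 0.2 to 0.5. Baseline SD s0: 3 or 4. Follow-up SD s1: 9.2 as in the Sample size section, or 5 as an alternative.

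**Step 1. The plan's own figure.** With 5.9 and SD 9.2, 80% power needs 39 per arm (normal approximation), or 39/0.75 = 52 with loss. The stated 60 is not reproduced exactly, but 45 completers give 86.0% power for this contrast, so the stated beta below 0.2 is met for it. This calculation uses group means and an SD of 9.2, not the SD of a change score.

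**Step 2. Formulas (per-patient variance).**
- Change score: s0² + s1² − 2·rho·s0·s1
- Baseline-adjusted: s1²·(1 − rho²)
- Raw follow-up score: s1²

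The change-score variance minus the adjusted variance equals (s0 − rho·s1)², which cannot be negative. That is why adjustment never loses in large samples. The gain vanishes when s0 = rho·s1, that is, when the true slope rho·s1/s0 equals 1.

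**Step 3. What the entry cap allows.** Scores confined to 0 to 13 have an SD of at most 13/2 = 6.5, reached only if half the patients score 0 and half score 13. A baseline SD of 9.2 is therefore impossible in this trial.

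**Step 4. Adjusted variance against change-score variance.**

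| s0, s1 | rho 0.2 | rho 0.3 | rho 0.4 | rho 0.5 |
|---|---|---|---|---|
| 3, 9.2 | 81.25/82.60 = 0.98 | 77.02/77.08 = 1.00 | 71.10/71.56 = 0.99 | 63.48/66.04 = 0.96 |
| 4, 9.2 | 81.25/85.92 = 0.95 | 77.02/78.56 = 0.98 | 71.10/71.20 = 1.00 | 63.48/63.84 = 0.99 |
| 3, 5 | 24/28 = 0.86 | 22.75/25 = 0.91 | 21/22 = 0.95 | 18.75/19 = 0.99 |

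The reduction runs from about 0 to about 14%, or roughly 0 to 15%.

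**Step 5. Power for 5.9 points, 45 per arm, s1 = 9.2 (normal approximation).** With s0 = 3, the change score gives 87, 89, 91 and 93% at rho 0.2, 0.3, 0.4 and 0.5; the adjusted analysis gives 87, 89, 91 and 94%. With s0 = 4, the change score gives 86, 88, 91 and 94%. With SDs 3 and 5, both exceed 99%.

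**Step 6. If t0-tk means raw scores at each time.** The ratio of adjusted to raw variance is 1 − rho², that is 0.96 at rho 0.2 and 0.75 at rho 0.5. Adjustment still gains.

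**Step 7. Region.** In simulations with four arms, four regions and 45 completers per arm, and with region assumed to explain 0 to 5% of residual variance, adding region to the baseline-adjusted model changed power by about −0.2 to +1.2 percentage points. Type I error stayed near 5%.

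**Step 8. Cost.** One term for baseline and three for region: residual degrees of freedom fall from 180 − 4 = 176 to 172, and the critical t moves from 1.9735 to 1.9739. If all four terms were useless, the expected variance inflation would be about 1 + 4/170 = 1.02.

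**The case against.** The strongest objection is that the gain may be close to nothing. With baseline SD 3 and follow-up SD 9.2, the ratio lies between 0.96 and 1.00, and where it is essentially 1 the small-sample cost of about 2% could outweigh it. This stands, and it is why the point is a low-cost refinement and not a power deficit.

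A second objection is that multilevel regression is already planned and that its covariates may sit in a fuller document. That would hold if the confirmatory test had been deferred, but the article names it, and the multilevel regression comes afterwards without that status. A third is that t0-tk is terse and may not mean subtraction; adjustment gains under either reading.

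A reader might infer four stronger claims, which the protocol does not support.
- **A saving of 25 to 40% of patients, or power below 80%.** With equal SDs the ratio is (1 + rho)/2, or 0.60 to 0.75 at rho 0.2 to 0.5, and with SD 9.2 at both times change-score power for 5.9 points would be 67, 73 and 79% at rho 0.2, 0.3 and 0.4. The entry cap rules out a baseline SD of 9.2. Even at the limiting SD of 6.5, power falls just short of 80% only at rho 0.2 (79%).
- **Over-correction of chance baseline imbalance.** With SDs 3 and 9.2 the true slope would be 0.61, 0.92, 1.23 and 1.53 at rho 0.2, 0.3, 0.4 and 0.5. A forced slope of 1 may over- or under-correct, and nothing in the protocol fixes the direction.
- **Distortion from mode change or regression to the mean.** Table 1 lists PHQ-9 as "Researcher A (baseline) Online (follow-up sessions"), and the entry cap favours regression to the mean. Both apply to every randomised arm and cancel in expectation in the comparison between arms.
- **Bias from ignoring region.** Leaving region out after region-blocked allocation makes the test slightly conservative, not biased.

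**Conclusion.** The point holds as a free improvement. The confirmatory test is valid, but it is avoidably less efficient than the trial's own data allow, and it is loosely specified because two tests with different estimands are offered without a rule for choosing between them.

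That adjustment does not lose precision in large samples follows from algebra and needs no assumption about rho or the SDs. The size of the gain does need them. A variance reduction of roughly 0 to 15% over a change score rests on assumed baseline SDs of 3 to 4 with 9.2 at follow-up, or 3 with 5, at rho 0.2 to 0.5. The gain from region is small unless regions differ markedly, and the protocol gives no figure for how much they differ.

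**What to change.** In Analysis of clinical efficacy, name one primary model: follow-up PHQ-9 on arm, baseline PHQ-9 and region (fixed effect with four levels), fitted within the multilevel regression already planned and stated to be the confirmatory analysis. Report adjusted mean differences from ITAU with confidence intervals.

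Replace the open choice between ANOVA and Kruskal-Wallis with robust or bootstrap intervals around the same adjusted differences if residuals are skewed, so that the estimand does not depend on the data. Bring the one-way ANOVA sentence under Cost-utility analysis into line.

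The cost is wording and four degrees of freedom. No extra patients, visits or questionnaires are needed.

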### Sample size

According to the literature, with a standard deviation (SD) of 9.2 and a mean of 16.2 in the control group (ITAU) [30], 14.59 in the positive affect group [31], 16.12 in the healthy lifestyle group [32] and 10.3 in the mindfulness group [30], accepting an alpha of 0.05 and a beta risk < 0.2 in a bilateral contrast, and assuming a 25% patient loss to follow-up, we need 60 subjects in each condition. Therefore, the total sample size was determined at 240. This sample size also allows calculating clinically significant difference in the main outcome variable, PHQ-9 [29], and this difference has been placed at 5 points.

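### The confirmatory sentence covers all variables and names no PHQ-9 time point: tested visit by visit, PHQ-9 alone carries about a 10–14% false-positive risk, not 5%

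*Protocol article*

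**What the plan says.** All references are to the protocol article.

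- **Main outcome:** "The primary outcome will be depressive symptom severity assessed via PHQ-9". On timing: "It will be registered at four times: baseline, post-treatment, 6 month follow-up, and 12 month follow-up". None of the three follow-ups is singled out.
- **Secondary outcomes:** every other scale (SF-12, CSRI, EQ-5D, PANAS, FFMQ, PHI) stands under this heading.
- **Analysis of clinical efficacy:** the confirmatory sentence is "To confirm main hypothesis, all variables will be compared (t0-tk) using an analysis of variance (ANOVA) and post-hoc tests", with Kruskal-Wallis as the alternative. The same paragraph announces a head-to-head "comparison between the four groups" and states: "Intention-to-treat and per-protocol analysis will be used". Multilevel regression is to follow, with no stated role in the main test.
- **Cost-utility analysis, last lines:** "In all cases statistical significance corresponded to a value of p <0.05".
- **Sample size:** "accepting an alpha of 0.05 and a beta risk < 0.2 in a bilateral contrast", with a 5-point PHQ-9 difference. Neither is tied to a follow-up time or to a pair of arms.

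**The concern.** Two statements do not fit together. The outcome sections rank PHQ-9 above all other scales, while the confirmatory sentence puts every variable into the test of the main hypothesis. For PHQ-9 itself, the time point, which is part of the definition of a primary outcome, is left open among three.

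Post-hoc tests after an ANOVA can control error over the pairs of arms within one variable at one visit. They cannot control it across visits or across scales, and nothing else in the article does. A positive result at one of three visits could then be presented as confirmation at the 5% level when the real error rate is higher. Once the results are known, a choice of visit is no longer credible.

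**Working it through.** **Inputs.** From Sample size: 60 per arm, 25% loss, so 60 × 0.75 = 45 completers; SD 9.2; ITAU mean 16.2; mindfulness mean 10.3, a difference of 5.9; two-sided alpha 0.05. From Main outcome: three follow-ups. Four arms give 4 × 3 / 2 = 6 pairs, 3 of them against ITAU. Assumed, because the article does not give it: an equal correlation rho between visits, varied from 0 to 0.8.

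**The plan's own figure.** The article states no error rate over several tests, so there is none to reproduce. Its sample size uses one alpha of 0.05. The related size of 60 per arm is not recovered exactly: mindfulness v ITAU needs 39 completers, and 39 / 0.75 = 52. That is a separate matter and does not affect this point.

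**Three visits, error held at 5% within each.** If the visits were independent, the chance of at least one false positive would be 1 − 0.95³ = 14.3%. Correlation lowers it.

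**Simulation under the global null.** Four arms of 45, three visits, 24,000 replicates per row. Entries are the percentage of trials with at least one false positive on PHQ-9 over the three visits.

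| rho | Omnibus F at each visit | Tukey at each visit | 3 contrasts with ITAU × 3 visits, unadjusted | 6 pairs × 3 visits, unadjusted |
|---|---|---|---|---|
| 0 | 14.2 | 14.3 | 33.4 | 49.5 |
| 0.5 | 12.9 | 13.1 | 29.6 | 44.2 |
| 0.7 | 11.3 | 11.3 | 26.1 | 39.0 |
| 0.8 | 9.8 | 9.8 | 23.3 | 35.3 |

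A repeat with 60,000 replicates agreed within 0.6 percentage points; its extremes for the unadjusted columns were 23.4% and 49.1%. Post-hoc tests run only after a significant F give the same figures as the omnibus column under this null.

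**One visit only.** Omnibus F or Tukey: 4.7–5.2%. Three unadjusted contrasts with ITAU: about 12.5%. Six unadjusted pairs: about 20%.

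**Power cost of adjusting.** The standard error is 9.2 × √(2/45) = 1.940, and 5.9 / 1.940 = 3.042. By the normal approximation, power is Φ(3.042 − 1.960) = 86% at alpha 0.05 and Φ(3.042 − 2.394) = 74% at 0.05/3. The t-based values are 85% and 73%.

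**The case against.** The strongest reply is that this is a journal article, that the analysis plan is not shown, and that the name of a post-hoc test or a multiplicity method is commonly left to that plan. That stands: neither is counted here as missing. What remains is what the article states, namely confirmation over all variables for a trial with one main outcome and three unranked follow-ups. A later plan that confined confirmation to PHQ-9 at one visit would contradict that sentence, not fill it in.

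Other parts of the defence also stand:

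- The comparison from t0 to tk is ambiguous. Read as one repeated-measures test, the error rate would be near 5%. The text does not specify such a test, and the multilevel regression comes afterwards without a confirmatory role.
- The 0.05 rule closes the cost-utility section after a list of simple tests. It may refer to that list, and it is compatible with adjusted p-values. It is supporting evidence only.
- Whether three distinct programmes sharing one control need a joint 5% is debated. The 10–14% figure does not depend on that debate, because it comes from the three visits.

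A reader might infer more than the document supports:

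- **That the plan's error rate is as high as 44%.** This needs 18 pairwise t tests with neither an omnibus gate nor an adjustment. The article describes ANOVA followed by post-hoc tests.
- **That any significant contrast at any visit confirms the hypothesis.** No passage states this rule.
- **That every scale is tested at every follow-up.** Table 1 gives only PHQ-9 and SF-12 at all three; the other repeated measures are taken at 6 and 12 months.
- **That no primary outcome exists.** PHQ-9 is named; its time point is not.

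**Conclusion.** The point holds in limited form. The confirmatory sentence conflicts with the outcome hierarchy, and with three unranked PHQ-9 follow-ups the plan as written does not secure the 5% on which the sample size rests. If each follow-up is tested separately, the risk of a false positive on PHQ-9 is about 10–14%, two to three times the nominal level, even with good control within each visit.

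This assumes 45 completers per arm, no true difference between arms, and a between-visit correlation of 0 to 0.8. It would be roughly 23–49% only if the post-hoc tests were both unadjusted and ungated. It would also rise if other scales may confirm the hypothesis, or if the intention-to-treat and per-protocol results are treated as interchangeable; neither increase is quantified here.

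**What to change.** Rewrite the confirmatory sentence so that it covers PHQ-9 at one time point, chosen by the sponsor and named before unblinding. Test it by the four-group ANOVA with a post-hoc procedure that controls error over the contrasts: Tukey if all head-to-head pairs are to be confirmatory, or Holm for the three contrasts with ITAU. Remove the reference to all variables from that sentence. Label the other two PHQ-9 time points and all other scales secondary.

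The document gives no ground for preferring a particular visit: its 25% loss is not tied to a time point. Nor does it require that the planned active-against-active comparisons be demoted or that mindfulness be tested first. These choices are the sponsor's.

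The cost is mainly wording. The omnibus ANOVA at one time point keeps its power, about 84% with 45 per arm under the article's means. If the three contrasts with ITAU are Bonferroni-adjusted, power for mindfulness v ITAU falls from about 85% to about 73%. Restoring 80% would take 51 completers, or 51 / 0.75 = 68 randomised per arm (normal approximation).

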#### Descriptions of costing procedure

Data collection on the use and utilization of health and social services will be collected through the questionnaire Client Service Receipt Inventory (CSRI) Spanish version [40]. The variant to be used in this study was designed to retrospectively collect data on service use during the previous 6 months.

Costs were estimated from the healthcare and societal perspectives during the six months of follow-up. Direct health care costs were calculated by adding the costs derived from medication consumption, medical tests, use of health-related services, and cost of the staff running the CBT intervention.

The cost of medication will be calculated by determining the price per milligram according to the Databases of the drug from the Ministry of Health and Consumer and included the value-added tax. The total costs of medications were calculated by multiplying the price per milligram by the daily dosage used (in milligrams) and the number of days that the treatment was received. The main source of the unit cost data for medical tests and health services will be use the OBLIKUE database of health care costs. The OBLIKUE database contains information about Spanish healthcare service costs and was derived by systematic reviews of the literature; it consists of approximately 18,000 entries.

Indirect costs (lost productivity): Lost productivity will be calculated using the human capital approach, which involves multiplying the minimum daily wage in Spain for 2014 by the number of days of sick leave, as reported by each patient. Finally, total costs were calculated by adding the direct and indirect costs. Unit costs are expressed in Euros (€) based on 2014 prices.

In our study the general guidelines for conducting pharmacoeconomic analyzes in Spain and the International Society for Pharmacoeconomics and Outcomes Research (ISPOR) [47,48] will be followed.

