#### Secondary outcomes

Sociodemographic variables. Relevant sociodemographic information regarding gender, age, marital status (single, married/relationship, separated/divorced, and widowed), education (years of education), occupation, economical level will be collected.

Mini-International Neuropsychiatric Interview (MINI). This is a short structured diagnostic psychiatric interview that yields key DSM-IV and ICD-10 diagnoses [35]. MINI can be administered in a short period of time and clinical interviewers need only a brief training. It will be registered at baseline using its Spanish validated version [33].

SF-12 Health Survey [36]. This instrument consists of 12 items that measure the health-related quality of life. A psychometric analysis suggested that it has adequate psychometric properties and a validated Spanish version [37].

Client Service Receipt Inventory [38] (CSRI-Spanish version) [39]. Questionnaire for collecting information about use of healthcare and social care services and other economic impacts (such as time off work due to illness). The variant used in this study was designed to collect retrospective data on service utilization during the previous months after the last assessment. Data on baseline assess the previous six months before inclusion.

EuroQoL-5D questionnaire (EQ-5D – Spanish version) [40]. Generic instrument of health related quality of life. It has two parts: Part 1 records self-reported problems in each of five domains: mobility, self-care, usual activities, pain/discomfort and anxiety/depression. Each domain is divided into three levels of severity corresponding to no problems, some problems and extreme problems, which allows obtaining a population-based preference score or societal index (SI). A total of 243 theoretically possible health states can be obtained and the SI is calculated on the basis of these health states. Values range from 1 (best health state) to 0 (death). However, this index may also provide negative values that correspond to health states perceived as worse than death-. Utility scores for these health states were assigned using the readily available Spanish population tariffs [41]. Part 2 records the subject’s self-assessed health on a VAS, a 10 cm vertical line on which the best and worst imaginable health states score 100 and 0 respectively.

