##### Analysis perspective and time horizon

The perspective used in our analysis will be twofold: on one hand the social perspective, to include all costs and quality of life and moreover the perspective of the national health system.

The time horizon of the study is 12 months, so there will have to use any kind of discount or costs or profits.

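### The societal total, as itemised, is health-care cost plus sick leave: social-care use is collected but not costed, although the social perspective is said to include all costs

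*Protocol article*

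**What the plan says.** Three parts of the protocol article bear on this.

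**Collection.** Table 1 gives the assessment area of the Client Service Receipt Inventory (CSRI) as "Health and social services use". The Secondary outcomes section describes it as a "Questionnaire for collecting information about use of healthcare and social care services and other economic impacts", with time off work as an example of the latter. The costing section opens in the same way: "Data collection on the use and utilization of health and social services will be collected through the questionnaire Client Service Receipt Inventory (CSRI) Spanish version".

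**Perspective.** The costing section commits to two perspectives: "Costs were estimated from the healthcare and societal perspectives during the six months of follow-up". The section on analysis perspective and time horizon repeats the pair and defines the wider one as "the social perspective, to include all costs and quality of life", alongside the perspective of the national health system.

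**Summation.** The direct side is itemised: "Direct health care costs were calculated by adding the costs derived from medication consumption, medical tests, use of health-related services", and the staff cost of the intervention. The indirect side is days of sick leave valued at the minimum daily wage. Then: "Finally, total costs were calculated by adding the direct and indirect costs". Unit prices come from a ministry drug database for medication and, as main source, from the OBLIKUE health-care cost database for tests and health services.

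**The concern.** The definition of the social perspective and the list of costs that should deliver it do not match. One category that the trial collects, social-care use, appears in neither the direct nor the indirect term, and no price source is given for it. Two patients with the same health-care use and sick leave but different social-care use would receive the same societal total.

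Cost-effectiveness is part of the trial's rationale, and the Cost-utility analysis section builds the ICERs and acceptability curves on incremental cost. If the itemised sum is followed, the result reported as societal is narrower than its label. Any between-arm difference in social-care use is then lost from it, although the data are there.

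**Working it through.** The article states no figure to reproduce, so the check sets the components side by side.

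| Component | Recorded in the trial? | In the itemised sum? | Price source named? |
|---|---|---|---|
| Medication | yes | direct | drug database |
| Medical tests | yes | direct | OBLIKUE (main source) |
| Health-related services | yes, CSRI | direct | OBLIKUE (main source) for health services |
| Intervention staff | delivered by the trial | direct | none stated |
| Sick leave | yes, patient report | indirect | 2014 minimum daily wage |
| Social-care services | yes, CSRI | not listed | none stated |

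1. Let *H* be the four direct items, *I* sick-leave days times the minimum daily wage, and *S* the cost of social-care services.
2. Total as itemised: *T* = *H* + *I*.
3. Total implied by a perspective that includes all costs, limited to what the CSRI collects: *T*\* = *H* + *S* + *I*.
4. Difference per patient: *T*\* − *T* = *S*.
5. For two arms with incremental costs Δ*H*, Δ*S*, Δ*I* and incremental QALYs Δ*Q*, the ICER as itemised is (Δ*H* + Δ*I*)/Δ*Q*, and with social care it is (Δ*H* + Δ*S* + Δ*I*)/Δ*Q*. The difference is Δ*S*/Δ*Q*.

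Step 5 fixes what matters. The ICER changes only through the between-arm difference Δ*S*, not through the level of social-care cost. If the arms use social care equally, Δ*S* = 0 and the ICER is unchanged. If they differ, the direction of the change follows the signs of Δ*S* and Δ*Q*. The article gives neither quantity, so Δ*S*/Δ*Q* cannot be evaluated.

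**The case against.** The strongest reply is that the article does not actually exclude social care.

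- **The itemised sentence defines direct health-care costs, while the total refers to direct costs without that qualifier.** This is true, and it rules out the stronger reading that the plan expressly discards all recorded social-care cost. But no other direct category is defined anywhere, so a reader who follows the text has nothing else to add.
- **Health-related services might be meant broadly enough to cover social care.** The item stands under direct health-care costs, and the article names social services apart from health services in Table 1, in the CSRI description and in the costing section. On the broad reading, social care would also enter the health-care total, and nothing says how to remove it for the national health system perspective. The two totals would still need separating.
- **OBLIKUE is only the main price source, and a short article leaves the full unit-cost list to another document.** Both points are fair, and a missing price list is not a finding here. What remains is that the stated components are narrower than the stated perspective. That is a mismatch between two statements, not an omitted detail.
- **The population is mild to moderate depression in primary care, with dementia and brain pathology excluded, so heavy social-care use is not an obvious expectation.** This stands. It limits the likely importance of the point but does not remove the inconsistency.

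**Conclusion.** The inconsistency holds: the social perspective is said to include all costs, social-care use is collected, and the only components defined are health-care costs and sick leave. The conclusion rests on the plain reading that the direct costs in the total are the direct health-care costs just itemised.

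The size is unknown. A reader might infer a material bias by supplying amounts. For example, an assumed between-arm social-care difference of EUR 20 to 100 with an assumed QALY difference of 0.02 to 0.05 would shift the ICER by 20/0.05 = EUR 400 to 100/0.02 = EUR 5,000 per QALY. The documents support none of these inputs. The upper end pairs the largest assumed cost gap with the smallest assumed QALY gain, and a zero or negative Δ*S* is equally compatible with the text. The example shows only how the ratio behaves.

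The point concerns one component of one of two perspectives in a secondary economic analysis. The primary PHQ-9 comparison and the sample size are untouched. On the plain reading, so is the health-system ICER. It should be corrected because correction is cheap and the label would otherwise mislead, not because a large effect has been shown.

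**What to change.** In the costing section, define two totals:

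1. **National health system:** medication, medical tests, health services and intervention cost.
2. **Societal:** total 1, plus the social-care services recorded in the CSRI, priced from a named public tariff, plus lost productivity.

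State in the section on analysis perspective that the second total is the one used for the social perspective.

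If social care is not to be costed, remove the claim to include all costs and call the perspective health-care cost plus sick-leave productivity loss. That also resolves the inconsistency, but gives a narrower result.

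The first option costs a few lines of analysis text and a short list of extra unit costs. The second costs wording only. Neither needs new data collection, because the CSRI already records the use.
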